## Methods

### Design

A randomized controlled trial is performed including 3 parallel conditions: 2 experimental conditions (AAF and eMBCT) and a minimal intervention control condition. The intervention period is 9 weeks for all 3 conditions. Both experimental conditions are made as similar as possible in terms of time-investment and contact intensity with the therapist. Outcomes are self-reported and are Web-assessed at baseline (T0), 2 weeks post-intervention (T1), and at 6 months (T2) and 12 months (T3) after baseline. Figure 3 shows a schematic summary of the trial design.

The baseline assessment consists of 3 time-points: (1) T0a, the assessment to check eligibility; (2) T0b, the main baseline assessment taken after the eligibility check and informed consent, but naive of condition; and (3) T0c, directly after randomization for assessing the participant’s credibility and expectancy about the condition. All participants are invited to fill out short questionnaires in weeks 1, 2, 3, 4, 6, and 9 (Mi) of the intervention period in order to study mediation of the interventions.

After T2, patients in the control condition are offered 1 of the 2 experimental interventions, again in a research setting. Please note that the first 4 participants of this trial were randomized to 1 of the experimental conditions for the second semester, but to minimize dropout, all other patients will be allocated based on their own preference. During this second intervention period, these participants will again be assessed in weeks 1, 2, 3, 4, 6, and 9 (Mi’), the second week after the intervention (T1’), and 6 months after the second allocation (T2’). Participants in the control condition that are preferentially allocated to eMBCT after T2 do not wear the accelerometer during the second semester.

The protocol allows delay within the intervention period of a maximum of 2 weeks in case of, for example, illness or holiday. For all participants, the duration of their participation is approximately 12 months. Additional qualitative feedback will be obtained through explorative interviews with a subset of participants in the experimental condition shortly after T1 or T1’.

This trial was approved by the Twente Medical Ethical Committee (Enschede, the Netherlands) under number P12-26 and has been registered at The Netherlands National Trial Register under number NTR3483 [42].

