#### Randomization

If the eligibility-criteria are met, the researcher confirms the participant’s enrollment. Subsequently, the activity sensor is given to the participant and its setup is explained in a face-to-face meeting in the participant’s home or another mutually convenient location. The second baseline assessment starts (T0b), followed by randomization of the participant to 1 of the 3 conditions by a script embedded in the researchers’ Web portal and uses the random function of php (rand(1,3)) [50]. The researchers can neither influence nor predict the outcome of the randomization process. Subsequently, the researcher emails the participant about the outcome of randomization, requests the participant to complete the third baseline assessment (T0c), and assigns the participant to a therapist in case the participant has been randomized to an experimental condition. Participants who do not fill out T0c are considered as not being included. The allocation of a therapist is based on current availability of the therapists who are involved in the trial.

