#### Perceived Ability to Work

The work ability score, which is assessed with the first question of the work ability index [62,63], will also be used as an outcome parameter. It asks: “Imagine that your working ability in the best period of your life is rated 10 points. How would you rate your working ability at the present moment?” It is assessed at T0b, T1, T2, and T3.

Working hours and the level of absenteeism are assessed with questions from the Trimbos and iMTA questionnaire on costs associated with psychiatric illness (TiC-P) [64]). These will be assessed at T0b, T2, and T3.

**Table 2 table2:** Assessments of outcome measures and potentially mediating factors.

Outcome Measures and Potentially Mediating Factors		Parameters	T0^a^	Mi/Mi’^b^	T1/T1’	T2/T2’	T3
Primary outcome	Fatigue severity	CIS fatigue severity subscale: 8 items on a 7-point Likert scale.	a, b	3,6,9	x	x	x
Secondary outcomes	Other dimensions of fatigue	CIS physical and cognitive fatigue and motivation subscales: 4 items for each subscale, all on a 7-point Likert scale.	b		x	x	x
	Affect	PANAS: 20 items on a 5-point Likert scale.	a		x	x	x
	Psychological distress	HADS: 14 items on a 4-point scale.	a		x	x	x
	Self-perceived ability to work	Work ability score: 1 item on a 0-10 numeric rating scale (NRS).	b		x	x	x
	Return to work and working hours	Adapted questions of the TiC-P.	b			x	x
Primary mediating factors	Mindfulness	Freiburg Mindfulness Inventory short form [65,66]: 14 items on a 4-point Likert scale.	b	3,6,9	x	x	x
	Physical activity (PA)	Accelerometer: ProMove 3D [52]. Both summative PA and daily PA decline will be considered.	b	3,6,9^c^	x		
	Sleep quality	Subjective Sleep Quality Scale [67]:15 items (yes/no), and 1 self-conceptualized item (yes/no) that translates into: “Did you use sleep medication?”	b	3,6,9	x	x	x
	Sense of control over fatigue	Self-Efficacy Scale [56]: 7 items on a 4-point Likert scale.	b	3,6,9	x	x	x
	Credibility and expectancy	Credibility and Expectancy Questionnaire [68]: 6 items of which 4 are on a 9-point Likert scale, and 2 items on a 0-100 NRS.	c, c’	1,2,4			
	Working alliance	Working Alliance Inventory short form [69,70]: 12 items on 5-point scale; subscales: goal, task, bond.		1,2,4			
Secondary mediating factors	Perceived physical activity	Four self-conceptualized questions on perceived activity volume, comparative volume, and satisfaction with volume.	b		x	x	x

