	Self-efficacy on activities	Selected items from the self-efficacy scales of Bandura [71] and Rodgers [72,73]: 13 items on a 0-100 NRS; subscales: planning and coping.	b		x		
	Catastrophizing	Fatigue Catastrophizing Scale [74,75] 9 selected items on a 5-point Likert scale.	b		x		
	Fear of cancer recurrence	Two selected items on a 7-point Likert scale [76].	b		x		
	Causal attributions	One self-conceptualized open answer question that translates to: “What do you consider as the cause of your fatigue?”	b		x		

^a^Baseline assessment T0 consists of 3 time-points: T0a: before eligibility check, T0b: after inclusion, and T0c: after randomization. T0c’ is assessed after preferential allocation.

^b^Mi and Mi’ = assessments at week (i=) 1, 2, 3, 4, 6, 9 of the intervention

^c^All physical activity measurements are blind except for the experimental activity feedback condition at M3, M6, and M9. In the second semester, M3’, M6’, and M9’ do not include a physical activity measurement in the mindfulness condition.

**Table 3 table3:** Other assessments.

Demographics, medical history, and control factors	T0^a^	T1/T1’	T2/T2’	T3
Age, gender, education, family status, nationality, time since diagnosis, time since previous treatment, fatigue duration, psychological counseling in the past, comorbidity.	a			
Cancer type, cancer treatment, perceived life threat of cancer (7-point Likert scale), known heredity of cancer (yes/no/don’t know), former experience with attention focusing exercise (yes/no), religious beliefs, perceived social support (Multidimensional Scale of Perceived Social Support [77]: 12 items on a 7-point Likert scale).	b			
Medication use, substance use (caffeine, nicotine, alcohol, drugs), quality of life (1 item on a 0-10 NRS).	a	x	x	x
Pain intensity and limitations by pain (2 items on a 7-point Likert scale), body mass index.	b	x	x	x
Life events since previous assessment, professional help received for fatigue outside the scope of the study protocol.		x	x	x
Perceived effectiveness of the intervention (5 items of which 1 item 0-10 NRS and 2 yes/no questions), perceived social support in following the intervention (1-10 NRS).		x		
Social desirability: 6 selected items from the Balanced Inventory of Desirable Responding [78] on 5-point Likert scale.			x	

^a^Baseline assessment T0 consists of 3 time-points: T0a: before eligibility check; T0b: after inclusion; and T0c: after randomization.

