##### Mediators

###### Overview

The analysis of the mediators of the experimental conditions can be roughly subdivided into two steps: first analyze the primary factors individually for their longitudinal correlations with the outcome (Step 6), then combine the relevant factors in a multivariate analysis (Step 7). The specific hypothesis on the mediating factors of the interventions in this study are shown in Textbox 2.

###### Step 6

For analyzing the mediators of the experimental conditions, first we want to see whether there is a correlation between the growth trajectories of our outcome parameter and the potential mediator over time. The hypotheses considering mediators are shown in Textbox 2. The combined data from the participants in the first semester and data from the preferentially assigned participants in the second semester will be used.

The following subhypotheses will be tested for each primary mediator (these are also shown in Figure 5):

Is the growth of the primary outcome (Sy) for the entire study population correlated with growth of the potential mediator (Sz)?Is such correlation independent of group?Does the potential mediator change over time in the specific group, so is the slope factor (Sz) substantially unequal to zero?Is the slope factor in the specific group substantially greater than the slope factors in the other groups?

In these 4 subhypotheses, the first is congruent with testing the “conceptual theory” in classical mediation analysis, and subhypothesis 3 with testing the “action theory.” If subhypotheses 1-4 all are true, the factor will be considered a specific mediator for that intervention. If subhypotheses 1, 2, and 3—but not 4—are true, the factor will be considered a general mediator for fatigue severity. If either subhypothesis 1 (conceptual theory) or 3 (action theory) is false, the factor will not be considered a mediator.

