Hypotheses on mediators.We expect that, for AAF, increasing mean cumulative daily physical activity and reductions of daily physical activity decline are specific mediators.We expect that, for eMBCT, developing mindfulness skills is a specific mediator.We expect that sleep quality, working alliance, sense of control over fatigue, credibility, and expectancy are generic mediators for both e-therapies.The mediating role of the following factors will be explored: number of sessions completed, changes in causal attributions [99], decreased catastrophizing thoughts about fatigue [8], decreased fear of cancer recurrence [100,101], changes in perceived activity [102], increased self-efficacy on physical activity [103].

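### Step 6 tests only slopes, so it can wrongly reject credibility, expectancy and working alliance, which are first sampled after the arm is known or therapy has begun

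*Protocol article*

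**What the plan says.** Step 6 (Mediators) puts four subhypotheses to each primary mediator and exempts none:

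1. The mediator's slope Sz correlates with the fatigue slope Sy in the whole study population.
2. That correlation does not depend on group.
3. Sz differs from zero in the group concerned.
4. Sz is larger there than in the other groups.

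The article equates subhypothesis 1 with conceptual theory and subhypothesis 3 with action theory, and adds the exclusion rule "If either subhypothesis 1 (conceptual theory) or 3 (action theory) is false, the factor will not be considered a mediator". Step 7 then starts from the primary mediators that passed Step 6 and were also assessed in controls.

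Textbox 2 sets out the hypothesis at stake: "We expect that sleep quality, working alliance, sense of control over fatigue, credibility, and expectancy are generic mediators for both e-therapies".

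On timing, the Design section describes "T0c, directly after randomization for assessing the participant’s credibility and expectancy about the condition". The Randomization section has the researcher email the allocation before asking for T0c. For the second semester, the footnote to Table 2 says "T0c’ is assessed after preferential allocation". Table 2 gives working alliance no T0 entry, only weeks 1, 2 and 4.

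**The concern.** A slope carries the treatment's effect on a mediator only if the series starts before the treatment can act. Credibility and expectancy can respond to the allocation email itself. An alliance can form in the first week. If the effect then holds steady, Sz is near zero even though treatment changed the factor, and subhypothesis 3 fails.

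The plan would then report that a therapy working through raised expectancy or a good early alliance does not work through them. For credibility and expectancy the error carries forward, because Step 7, whose a path could show a difference in level, takes only primary factors that passed Step 6. Mediation is the trial's second stated objective.

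**Working it through.** The article gives no figure for this rule, so there is none to reproduce. The check sets schedule against rule, then sizes the consequence.

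**1. Schedule (Table 2, Design, Randomization; first semester)**

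| Primary mediator | First sample | Later samples | Arm known at first sample? |
|---|---|---|---|
| Mindfulness, sleep quality, sense of control | T0b | weeks 3, 6, 9; T1, T2, T3 | no |
| Physical activity | T0b | weeks 3, 6, 9; T1 | no |
| Credibility and expectancy | T0c | weeks 1, 2, 4 | yes |
| Working alliance | week 1 | weeks 2, 4 | yes, and therapy has begun |

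**2. Rule.** Subhypotheses 1, 3 and 4 concern Sz, and 2 concerns the slope correlation. The level Iz appears in Figure 5 but in no subhypothesis.

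**3. Chance that subhypothesis 3 passes.** Suppose the arm raises the mediator by d (in between-person SDs). A share s is present at the first sample and the rest builds linearly over T weeks.

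- Mean slope = d(1 − s)/T.
- Standard error = √(σ²/S + τ²)/√n, where S is the sum of squared deviations of the sampling times.
- Assumed, not in the article: residual SD σ = 0.5, slope SD τ = 0.05 per week, two-sided alpha .05.
- n = 198/3 = 66, from the article's 198 completers, split equally for illustration.

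Credibility and expectancy (0, 1, 2, 4): S = 8.75, T = 4, standard error = √(0.25/8.75 + 0.0025)/√66 = 0.1763/8.124 = 0.0217.
Working alliance (1, 2, 4): S = 4.667, T = 3, standard error = 0.2368/8.124 = 0.0291.

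For example, with d = 0.5 and s = 0.5 at times 0, 1, 2, 4, the slope is 0.0625. Its ratio to the standard error is 0.0625/0.0217 = 2.88, which gives 81%.

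| Share present at first sample | Credibility/expectancy, d = 0.5 / 0.8 | Alliance, d = 0.5 / 0.8 |
|---|---|---|
| 100% | 5% / 5% | 5% / 5% |
| 75% | 30% / 62% | 29% / 62% |
| 50% | 81% / 99.5% | 80% / 99.5% |
| 0% | 100% / 100% | 100% / 100% |

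A simulation of 2,000 runs per cell agreed to within about 2 percentage points.

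**4. Full rule against a level test.** Simulation of expectancy, 2,000 runs: 77 treated and 94 controls (the article's expected T2 counts), d = 0.5, slope SD 0.1, error SD 0.5, fatigue slope = −0.05 × driver + noise (SD 0.08), with per-person least-squares slopes standing in for latent slopes. Step 6 means subhypotheses 1 and 3 both at p < .05. The level test means an arm difference at T0c, plus T0c level predicting Sy with arm in the model.

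| What drives fatigue | Share at T0c | Step 6 accepts | Level test accepts |
|---|---|---|---|
| T0c level (true mediation) | 100% | 0.2% | 82% |
| Week-4 value (true mediation) | 50% | 31% | 31% |
| Week-4 value (true mediation) | 0% | 45% | 6% |
| Stable trait only (no mediation) | 100% | 0.5% | 81% |

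Neither test covers all mechanisms, and the last row shows that the level test cannot tell mediation from a stable trait.

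**The case against.** Step 6 states that it looks for correlated growth, so slopes are its declared target, and the plan says it is written in general terms. That explains the choice but does not remove the fault, because the rule draws a definite conclusion (not a mediator) from slopes alone.

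A reader might infer that Step 6 always misses these mediators. The documents do not support that. Nothing in them says the three factors stay flat after the first sample, and subhypothesis 3 passes readily once a good part of the effect builds later. The near-zero acceptance in the first simulated row follows from its assumptions: full effect at T0c, with level driving fatigue. This objection stands and limits the claim to what the rule can do.

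A reader might also conclude that the T0c level should replace the slope. That would lose effects that build during therapy (6% against 45% above) and would accept a stable trait such as optimism as a mediator in about 81% of runs. This also stands.

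On working alliance, the article assigns therapists only to the experimental arms and gives controls standard emails. Step 7 already leaves out factors not assessed in controls. If alliance is one of these, Step 6 does not cause its absence from Step 7. Nor is subhypothesis 4 needed for the generic label, and it can still compare AAF with eMBCT. What remains is that Step 6 would be alliance's only test, with subhypothesis 1 defined on a population part of which has no alliance data.

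**Conclusion.** The point holds as a conditional one. The timing facts and the wording of the rule are plain in the article, and together they mean that Step 6 cannot see an effect already present at the first sample. Credibility, expectancy and working alliance, three of the five hypothesised generic mediators, can be wrongly rejected. For credibility and expectancy the rejection also closes Step 7.

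The size depends on an unknown, the share of the effect present at first sampling: subhypothesis 3 passes in about 5% of trials if all of it is, and about 80% if half of a 0.5 SD effect is. Effect sizes, variances and the mechanism linking mediator to fatigue are assumptions. The primary effectiveness analysis is unaffected. The rule should be corrected before the mediator analysis, since as written it fixes negative conclusions on named hypotheses in advance.

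**What to change.** **Credibility and expectancy.** Keep the slope tests and add a level test beside them:

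- Action theory: T0c level, intervention versus control, in first-semester randomized data only, because T0c′ follows the participant's own choice for almost all former controls.
- Conceptual theory: T0c level predicting Sy with arm in the model.

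Do not declare either factor a non-mediator on the slope alone. Let it enter Step 7 if the level test or the slope test is met.

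**Working alliance.** If it is not assessed in controls, test its early level and its slope as process predictors of later fatigue within AAF and eMBCT only. Restrict subhypothesis 1 to those two arms and subhypothesis 4 to AAF versus eMBCT. Do not label it a mediator versus control.

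**Other primary mediators.** Keep the present rule, since their series start at T0b.

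**Cost.** The change is to analysis wording. It needs no new measurement, and T0c exists for everyone counted as included, because the Randomization section does not count those who skip it. It adds a test per factor and some multiplicity. Without a pre-allocation sample, the level-to-fatigue path is confounded by stable traits, so it must be reported as an association and not as proof of mediation.

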**Figure 5 figure5:**
[figure not shown]
Simplified representation of a correlated growth model in which Iy and Sy represent the intercept and slope factors of the latent growth model of the outcome parameter, and Iz and Sz represent the latent growth factors of the mediator. H1-4 represent the 4 subhypotheses of Step 6. All indicators have been left out for clarity.

###### Step 7

The next step in studying potential working mechanisms is a single-step, multiple-mediation analysis using structural equation modeling [104-106]. By estimating such a model, we expect to obtain a comprehensive model for all the working mechanisms of the intervention. It should be noted that this model assumes that an intervention works in the same way for all participants in a particular group [107]. Again, data from both semesters will be used.

A separate model will be tested for each intervention. Each model will have the following paths (Figure 6), where X=independent variable (1/0 for specific intervention vs control group), Y=outcome variable (difference score T2-T0b of the primary outcome measure), and Z=mediator:

a: X regressed on Z.b: Z regressed on Y;c’: direct effect of X on Y.

For each experimental intervention, the starting model will consist of all the significant primary mediators of Step 6 that have also been assessed in the control group. In other words, the factors that have shown to be mediators in the correlated growth model will be the starting point for this model. The models will then be complemented with the secondary mediating factors described in Textbox 2. Mediating factors for which the indirect effect (a × b) is insignificant will be removed stepwise, after which a final model will be created.

Model fit, standardized path coefficients—including indirect effects—and the total effect of at least the first and final models will be reported with 95% confidence intervals.

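### Step 7 sets one mediation outcome, T2-T0b, for data from both semesters; applied as written, former controls treated after T2 carry a fatigue change from before their treatment

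*Protocol article*

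**What the plan says.** Step 7 (Analysis Plan, Mediators) fits a separate multiple-mediation model for each intervention. The exposure is "X=independent variable (1/0 for specific intervention vs control group" and the outcome is "Y=outcome variable (difference score T2-T0b of the primary outcome measure". No other outcome definition is given. On the data, the step says "Again, data from both semesters will be used". The word Again points back to Step 6, where, besides the first-semester data, "data from the preferentially assigned participants in the second semester will be used".

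The Design section says who these second-semester participants are and when their treatment starts: "After T2, patients in the control condition are offered 1 of the 2 experimental interventions, again in a research setting". It labels their later assessments with primes: Mi', T1' and T2', the last of these six months after the second allocation. A footnote to Table 2 adds one primed baseline assessment: "T0c’ is assessed after preferential allocation". Table 2 lists no T0b'.

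The path definitions in Step 7 read "a: X regressed on Z.b: Z regressed on Y", with c' as the direct effect of X on Y.

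**The concern.** The outcome formula and the data rule do not fit together. For a former control who takes up an intervention after T2, both T0b and T2 precede that intervention. T2-T0b is then the change under psycho-educational emails, whatever the later treatment does.

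If that value is entered with X=1, three things follow:

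- The record cannot carry any treatment effect, so the treated group's mean change is pulled toward the control mean.
- The same person has the same Y in the control record and in the treated record.
- Path b relates a second-semester mediator change to a fatigue change that came before it. The article presents the time ordering of mediators and fatigue as a strength of the design (Discussion, Principal Findings).

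Mediation is the trial's second stated objective, so the outcome definition in this step matters even though it is not the primary analysis.

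**Working it through.** **1. Which change the formula names.** For each type of record:

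| Record | Treatment period | T2-T0b covers | Change over the treated semester |
|---|---|---|---|
| First semester, experimental arm | T0b to T2 | the treated semester | T2-T0b |
| First semester, control arm | none | the control semester | (control) T2-T0b |
| Second semester, former control | T2 to T2' | the control semester | T2'-T2 |

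Adding primes does not repair the formula, because no T0b' exists. Replacing only T2 by T2' gives T2'-T0b, which spans the control semester and the treated semester together. The last scheduled CIS fatigue score before second-semester treatment is T2.

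**2. How many records are involved.** Inputs from Power Analyses: 330 participants, 30% attrition in the experimental arms, 15% in the control arm, 30% dropout in the second semester, 10% later exclusion. The article's own figures reproduce:

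- Per arm: 330 / 3 = 110.
- Experimental arm after attrition: 110 × 0.70 = 77.
- Control arm at T2: 110 × 0.85 = 93.5, stated as 94.
- Second-semester completers: 94 × 0.70 = 65.8; split equally, 65.8 / 2 = 32.9, about 33 per intervention.
- Completers per intervention: 77 + 33 = 110, as stated.
- After exclusions: 2 × 110 × 0.90 = 198, as stated.

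The stated 110 is reached only by counting about 33 second-semester completers in each intervention, so the equal split is implied by the article. The affected share is 33 / 110 = 30%. A uniform 10% exclusion does not change it.

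**3. Range of the share.** Second-semester allocation is by preference. Assume that between 25% and 75% choose a given intervention:

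- 25%: 65.8 × 0.25 = 16.45; 16.45 / (77 + 16.45) = 18%.
- 75%: 65.8 × 0.75 = 49.35; 49.35 / (77 + 49.35) = 39%.

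**4. Effect on the total effect.** Let D be the true treated-minus-control difference in change. Assume that former controls who complete the second semester had, on average, the same control-semester change as all controls. Then

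expected total effect = (77 × D + 33 × 0) / 110 = 0.70 D.

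Over the range in item 3 the multiplier is 1 - 0.18 = 0.82 to 1 - 0.39 = 0.61.

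**5. Effect on the paths.** An illustration by simulation used 2,000 data sets with 94 control, 77 first-semester treated and 33 second-semester treated records. The standardized paths were assumed: a = 0.5, b = -0.5, c' = -0.25. Second-semester mediator changes were drawn independently of the earlier fatigue change.

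| Quantity | Y = T2'-T2 for second-semester records | Y = T2-T0b for all |
|---|---|---|
| Total effect | -0.50 | -0.35 |
| Indirect effect (a × b) | -0.25 | -0.21 |
| Direct effect (c') | -0.25 | -0.14 |

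The total agrees with item 4: 0.70 × (-0.50) = -0.35. The split between direct and indirect effect depends on the assumed paths.

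**The case against.** The strongest reply is that T2-T0b is shorthand. The Introduction says the plan is written in general terms. Table 2 uses joint columns for T1/T1' and T2/T2', which treats the two semesters as parallel. Step 7 does not state the value of X for second-semester records; X=1 is an inference. The literal reading also gives one person identical outcomes under control and under treatment, which few analysts would intend. The authors may well have meant the change over the treated semester.

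Part of this stands. A reader might infer that the trial has decided to analyse a pre-treatment outcome; the documents do not show that intention, and the dilution holds only if the formula is applied literally. But the formula names specific visits, the article elsewhere uses primes to tell the semesters apart, and even the sympathetic reading leaves the second-semester baseline to be chosen. This is a stated rule that does not fit its data, not a detail left out for brevity.

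A reader might also infer from the path wording that the model runs backwards and would produce false mediators. The documents do not support that. Step 7 labels X the independent variable, Y the outcome and Z the mediator, and it tests a × b as the indirect effect. The Figure 6 caption repeats the roles. Only X to Z to Y is coherent with these labels, so the phrasing is a slip.

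Nor does the point reach the main result: Step 1 and the Figure 3 caption restrict the effectiveness analysis to first-semester data.

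**Conclusion.** The point holds in a limited form. As written, Step 7 gives second-semester treated records a control-semester outcome. With the equal split implied by Power Analyses this is about 30% of treated completers per intervention, and literal application would reduce the expected total effect to about 70% of its true value. With the assumed 25% to 75% preference range, the affected share is about 18% to 39%.

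These sizes rest on the planned attrition figures, on X=1 for the second-semester records, and on an average control-semester change among those who cross over. The direction does not depend on the exact figures: records whose outcome predates treatment can only dilute the total effect under these assumptions. The damage is confined to the mediation analysis, but the definition should be corrected before that analysis is run.

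**What to change.** Define Y in Step 7 by record: T2-T0b for first-semester records and T2'-T2 for second-semester records. State that second-semester treated records enter with X=1, and take each mediator change from the same semester as its Y. For fatigue this takes a sentence or two and no new data, because Table 2 schedules the CIS fatigue subscale at T2 and T2'.

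The mediators need one more rule. Mindfulness, sleep quality, sense of control and perceived physical activity are measured at T2, so T2 can serve as their second-semester baseline. Accelerometer activity, self-efficacy on activities, catastrophizing, fear of recurrence and causal attributions are not. For these, choose one of two options in advance:

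- Name T1, the last scheduled pre-treatment value, as the second-semester baseline. The cost is an older baseline: T1 falls about 9 + 2 = 11 weeks after the intervention starts and T2 at about 26 weeks, so it is roughly 15 weeks older, ignoring permitted delays. For accelerometer activity this can serve only those who choose AAF, since former controls choosing eMBCT do not wear the device in the second semester.
- Restrict these mediators to first-semester records. The cost is fewer records: about 77 instead of 110 treated completers per intervention, before the 10% exclusion.

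Because Step 7 is a joint model, also say how records lacking one mediator are handled.

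In passing, correct the path wording: a is Z regressed on X; b and c' come from Y regressed on Z and X.
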